## 8.3 Data Analysis Considerations

### 8.3.1 Analysis Populations

The ‘All Subjects’ population will be defined as all subjects randomised to nasal challenge sequence who had at least one nasal challenge. This population will be used for all listings, tables and figures.

### 8.3.2 Statistical Analyses

Each of the measures will be summarised descriptively by dose and time using appropriate summary statistics. If appropriate, response variables will be transformed (e.g. log-transformed). Gene expression data will be normalised by house-keeper gene. The TNSS will be calculated by summing the scores of nasal blockage, nasal discharge/rhinorrhoea, nasal burning/itching/pain sensation, and sneezing at each timepoint. Weighted means of symptom scores will be calculated over the time interval 0 to 10h.

TNSS, nasal sniff pressures, nasosorption measures and gene expression data from the nasal scrapes will each be plotted against time, with a separate plot for each subject and measure, and with LPS dose and placebo represented by separate lines on the plots. Summary statistics (e.g. mean +/- 95% confidence intervals or median and interquartile range) for nasal lavage and gene expression data will be plotted by dose against time.

Correlations will be explored using scatter plots for the following measures:

- Weighted means TNSS vs. maximum TNF-α
- Weighted means TNSS vs. maximum IL-8
- Weighted means TNSS vs. maximum s-ICAM-1
- Maximum ICAM-1 expression vs. maximum TNF-α

Reproducibility of the nasal LPS challenge for ICAM-1 expression and TNF-α will be explored using the following subsets of data:

- Predose data for each period to explore intra-subject variability.
  Parameter vs. period number will be plotted with a separate line for each subject to explore whether there is a period effect. Box and whisker plots will also be used to summarise the parameter by period.
- Placebo period data – Parameter vs time will be plotted with a separate line for each subject to explore whether there is a time-course effect. Box and whisker plots will also be used to summarise the parameter over time.

Box and whisker plots for ICAM-1 expression and TNF-α and dose and time will be presented to investigate whether these measures return to baseline after 24h.

Additional exploratory analyses may be performed to further characterize the expression profile of ICAM following nasal LPS challenge.

1. **Study Schedule**

|  | Screening | Sessions 1-5 | | | | | | | | | | | | | | Tel F/up |
| --- | --- | --- | --- | --- | --- | --- | --- | --- | --- | --- | --- | --- | --- | --- | --- | --- |
|  |  | -30m to  -15m | 0 | 30m | 1h | 2h | 3h | 4h | 5h | 6h | 7h | 8h | 9h | 10h | 24h |  |
| Medical interview and examination | X |  |  |  |  |  |  |  |  |  |  |  |  |  |  |  |
| Informed consent | X |  |  |  |  |  |  |  |  |  |  |  |  |  |  |  |
| Height & weight | X |  |  |  |  |  |  |  |  |  |  |  |  |  |  |  |
| BP & heart rate | X | X |  |  |  |  |  |  |  |  |  |  |  |  |  |  |
| Temperature – oral | X | X |  |  |  | X |  | X |  |  |  | X |  |  |  |  |
| Blood sample:  Haematology  Biochemistry | X |  |  |  |  |  |  |  |  |  |  |  |  |  |  |  |
| Pregnancy test | X | X |  |  |  |  |  |  |  |  |  |  |  |  |  |  |
| Drugs of abuse | X |  |  |  |  |  |  |  |  |  |  |  |  |  |  |  |
| ECG | X |  |  |  |  |  |  |  |  |  |  |  |  |  |  |  |
| Nasal lavage to both nostrils and discard (wait 10 mins before sampling) |  | X |  |  |  |  |  |  |  |  |  |  |  |  |  |  |
| Dosing LPS/placebo |  |  | X |  |  |  |  |  |  |  |  |  |  |  |  |  |
| Nasosorption  (Right Nostril) |  | X |  | X | X | X | X | X | X | X | X | X | X | X | X |  |
| Nasal Lavage  (Left Nostril) |  | X |  |  |  | X |  | X |  |  |  | X |  |  | X |  |
| Nasal scrape  (Left Nostril) |  | X |  |  |  |  | X |  |  | X |  |  |  |  | X |  |
| Modified total nasal symptom score, TNSS | X | X |  | X | X | X | X | X | X | X | X | X | X | X | X |  |
| PNIF | X | X |  |  |  | X |  | X |  |  |  | X |  |  | X |  |
| Systemic adverse events: fever, flu, mylagia |  | X |  | X | X | X |  | X |  | X |  | X |  |  | X | X |

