**2.2 Primary Objective**

The principal research questions (primary end point, PEP):

- Can we develop a well tolerated, robust and reproducible (validated) nasal LPS challenge system in terms of ICAM-1 induction ?
- Can we document a dose response and time course to nasal LPS in terms of cell influx, cytokine and chemokine release, and nasal epithelial curettage (Rhinoprobe) mRNA expression ?
- To assess the unstimulated expression of ICAM-1 in nasal epithelial scrapes.
- To provide a nasal challenge method with LPS to enable a “proof of target pharmacology” for a therapy directed against ICAM-1 induction. This may also permit dosage optimisation in relation to clinical efficacy studies.

1. **Study Design**

5-way crossover study, randomized, single-blind, placebo-controlled, dose-response to LPS.

A single cohort of 15 healthy volunteers will be studied in a 5-way cross-over study (4 doses of LPS versus placebo), for a minimum of 12 to complete.

A balanced Latin square randomized design will be used.

Total study duration: 6-9 months

1. **Study population**

For this clinical study it is proposed to study healthy volunteers with no history of allergy, nor any other significant illnesses or therapy.

15 healthy volunteers will be recruited, for a minimum of 12 to complete

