# Data Analysis and Statistical Considerations

## 8.1 Hypotheses

The primary objective for this study is to explore the effects of LPS challenge on ICAM-1 expression in healthy volunteers and determine a dose response relationship. This study is hypothesis generating rather than formal hypothesis testing.

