## 8.2 Study Design Considerations

### 8.2.1 Sample Size Assumptions

The study will recruit 15 healthy volunteers in order to ensure 12 subjects complete the study. Any replacement subjects will be assigned to the same regimen sequence as the subject that they are replacing.

No statistical techniques will be used to calculate the sample size. The sample will be based primarily on feasibility.

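### The planned group summaries are by dose only; a crossover with a dose-response objective should also report within-subject LPS-versus-placebo estimates

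*Protocol*

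**What the plan says.** The Study Design section of the protocol describes a "5-way crossover study, randomized, single-blind, placebo-controlled, dose-response to LPS", with four LPS doses and placebo given to every subject. Section 8.1 states the primary objective as to "explore the effects of LPS challenge on ICAM-1 expression in healthy volunteers and determine a dose response relationship", and adds: "This study is hypothesis generating rather than formal hypothesis testing".

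Section 8.3.2 lists these outputs:

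- Descriptive summaries of every measure by dose and time.
- Group plots for two kinds of data, with the summary statistic left open by example: "mean +/- 95% confidence intervals or median and interquartile range) for nasal lavage and gene expression data will be plotted by dose against time".
- Per-subject plots over time, with each LPS dose and placebo as its own line, for TNSS, sniff pressures, nasosorption measures (which include s-ICAM-1) and gene expression. Nasal lavage is not in this list.
- Box plots of ICAM-1 expression and TNF-α by dose and time, to see whether they return to baseline by 24h.
- Predose values by period and placebo-period values over time, to look at reproducibility.
- Optional further exploratory work on the ICAM profile, not described.

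On numbers, section 8.2.1 says: "The study will recruit 15 healthy volunteers in order to ensure 12 subjects complete the study". Replacements take the sequence of the subject they replace. Section 8.3.1 analyses everyone with at least one challenge: "This population will be used for all listings, tables and figures".

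**The concern.** Giving every subject all five treatments allows each person's LPS response to be set against the same person's placebo response, so that stable differences between people drop out. None of the listed group outputs uses this. The summaries treat one dose at a time, no LPS-minus-placebo quantity is named, and the predose values collected in every period serve the reproducibility plots but not the dose comparison.

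The stake is how the dose response will be read. By-dose curves with placebo among them invite the eye to compare bars. Bars that carry between-subject spread can overlap widely even when most subjects respond. Nasal lavage, the cell-influx readout, is most exposed, because it has neither a paired summary nor a per-subject plot.

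A second issue is who contributes to each mean. If only 12 of 15 complete and partial data are kept, the five dose means can rest on different subjects and an uneven mix of periods.

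**Working it through.** **Inputs from the protocol.** Five treatments per subject; 15 recruited, 12 to complete (section 8.2.1). No SD, correlation, effect size or power is given ("No statistical techniques will be used to calculate the sample size"), so there is no stated figure to reproduce.

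**Assumptions.** Results are in units of the SD of a single response, taken as equal across doses. The within-subject correlation between periods, ρ, is not in the protocol and is varied. n = 12 complete subjects.

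**Step 1: interval for one dose mean.** t(11)/√12 = 2.201/3.464 = 0.635 SD. Two such bars stop overlapping only when the means differ by 2 × 0.635 = 1.27 SD.

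**Step 2: dose-placebo difference read as two independent groups.** t(22) × √(2/12) = 2.074 × 0.408 = 0.847 SD.

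**Step 3: the same difference from a crossover model** with subject, period and dose. Residual df = 11 × 4 − 4 = 40. Half-width = t(40) × √(2(1−ρ)/12), with t(40) = 2.021.

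| ρ (assumed) | Crossover half-width (SD) | Ratio to 0.847 | Narrower by |
|---|---|---|---|
| 0 | 0.825 | 0.975 | 2.5% |
| 0.3 | 0.690 | 0.815 | 18.5% |
| 0.5 | 0.583 | 0.689 | 31% |
| 0.8 | 0.369 | 0.436 | 56% |

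**Step 4: sensitivity to the method.**

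- A simple paired t interval, t(11) × √(2(1−ρ)/12), gives 0.752 at ρ = 0.3 and 0.635 at ρ = 0.5. It beats the unpaired interval only when ρ exceeds 1 − (2.074/2.201)² ≈ 0.11; at ρ = 0 it is 0.899, or 6% wider.
- If the unpaired reading pools the variance over all five doses (55 df), its half-width is 0.818. The crossover gain is then 16% at ρ = 0.3 and 55% at ρ = 0.8, and at ρ = 0 the crossover interval is marginally wider (0.825).
- With 15 complete subjects (52 df) the pattern is the same: 0.748 unpaired against 0.613, 0.518 and 0.328 at ρ = 0.3, 0.5 and 0.8.

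**Step 5: balance.** In Table 1 each treatment occurs once in each period, with three subjects per sequence. With complete data, additive period effects therefore cancel from differences between raw dose means. Twelve completers cannot be spread equally over five sequences (12/5 = 2.4), so that cancellation is no longer exact for completers, and subjects with partial data contribute to some dose means only. The same imbalance makes the Step 3 widths for n = 12 slightly optimistic.

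**The case against.** Four points on the other side have force.

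1. *The intervals are not wrong.* A reader might infer that the planned error bars are erroneous. They are not: each is a valid interval for its own dose mean, and the protocol nowhere says they will be used to judge LPS against placebo. They are also only an example, with median and interquartile range as the alternative, and the sentence covers only lavage and gene expression. This stands. The bars are merely unsuitable for the comparison that the objective calls for.

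2. *Pairing is not ignored.* A reader might also infer that the plan treats the five doses as five groups of people throughout. The per-subject plots contradict that for TNSS, sniff pressures, nasosorption and gene expression, including both ICAM-1 readouts. This stands too, but the plots give no estimate or interval, and they omit lavage.

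3. *The study is exploratory and an SAP may exist.* A model could properly sit there, and its absence from a protocol is not an error in itself. However, section 8.3.2 is not silent: it lists the displays, and the group-level ones are all by dose. An exploratory aim removes the need for tests, not for estimates suited to the design. If the SAP already holds paired estimates, only the protocol wording needs aligning.

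4. *Size and bias are uncertain.* The gain rests on a correlation that the protocol does not give. A reader might infer that dropout will distort the dose means; the documents show only that it could. Table 1 is balanced, and same-sequence replacement helps to keep it so.

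**Conclusion.** The point holds as a recommendation for a better-suited summary, not as an error in a stated figure. For the trial's own dose-response question, by-dose summaries give up precision whenever ρ is clearly positive: about 18% to 56% of the interval width for ρ between 0.3 and 0.8 with 12 completers, and essentially nothing at ρ = 0. For positive ρ, reading the bars as a comparison errs towards missing an LPS effect, not towards a false one. The figures assume equal variance across doses and 12 complete subjects. The possible shift in dose means from incomplete data cannot be sized from the documents. The gap is widest for nasal lavage, where no planned display keeps the pairing.

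**What to change.** In section 8.3.2 (or the SAP, with the protocol aligned), at least for ICAM-1 expression, s-ICAM-1 and nasal lavage cells:

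- Estimate LPS minus placebo for each dose at each sampled time point, with 95% intervals, from a model with dose and period as fixed effects, subject as random effect and that period's predose value as covariate, in the All Subjects population. Report ratios where a log transform suits the measure; keep differences for scores or counts that can be zero.
- Report the trend over dose, and name the dose scale used, since placebo has no logarithm of dose.
- Use time-point values for these measures. The 0 to 10h weighted mean is defined in the protocol for symptom scores only, and lavage and scrapes have no 10h sample.
- Add a per-subject plot for nasal lavage, with all doses and placebo overlaid.
- Keep the raw by-dose summaries as support, and state that their intervals are not meant for comparing doses.

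No p-value is needed. The cost is a few lines of text and routine programming on data already being collected.

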# 2. Study Hypotheses and Objectives

The purpose of this study is to develop a safe and effective challenge model to LPS in terms of induction of ICAM-1, and so provide a robust framework for the clinical assessment of future anti-inflammatory therapies directed specifically against ICAM-1.

- 1. **Hypothesis**

The nasal ICAM-1, cellular and cytokine/chemokine responses will be reproducible and show a dose response in relation to the amount of LPS used to challenge.

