## Regimen Assignment

Subjects will be assigned to a sequence in accordance with the randomisation schedule generated prior to the start of the study. The randomisation will be balanced over the 5 nasal challenge sequences and will be generated using RandAll, the GSK web-server based clinical trials randomisation validated system.

A description of each challenge sequence is provided in Table 1. The LPS dose corresponds to the dose administered to each nostril.

Table 1. Nasal LPS Dosage Regimen Sequence

| Sequence | Number of subjects receiving sequence | Nasal Challenge 1 | Nasal Challenge 2 | Nasal Challenge 3 | Nasal Challenge 4 | Nasal Challenge 5 |
| --- | --- | --- | --- | --- | --- | --- |
| 1 | 3 | placebo | 1μg LPS | 10μg LPS | 30μg LPS | 100μg LPS |
| 2 | 3 | 1μg LPS | 30μg LPS | placebo | 100μg LPS | 10μg LPS |
| 3 | 3 | 10μg LPS | 100μg LPS | 30μg LPS | 1μg LPS | placebo |
| 4 | 3 | 30μg LPS | 10μg LPS | 100μg LPS | placebo | 1μg LPS |
| 5 | 3 | 100μg LPS | Placebo | 1μg LPS | 10μg LPS | 30μg LPS |

A washout time of 12-28 days will be employed between challenges

1. **Samples and Measures**

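### Reproducibility of the LPS challenge is to be explored from pre-dose and placebo data only, and no dose is repeated within a subject, so same-dose repeatability of the ICAM-1 response cannot be estimated

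*Protocol*

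**What the plan says.** The first question under Protocol section 2.2 is "Can we develop a well tolerated, robust and reproducible (validated) nasal LPS challenge system in terms of ICAM-1 induction". The hypothesis in section 2 is that "The nasal ICAM-1, cellular and cytokine/chemokine responses will be reproducible and show a dose response in relation to the amount of LPS used to challenge". Both concern the response that LPS induces.

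Section 8.3.2 opens its reproducibility paragraph with "Reproducibility of the nasal LPS challenge for ICAM-1 expression" and TNF-α, and restricts the exploration to two listed subsets. The first is "Predose data for each period to explore intra-subject variability", plotted by period for each subject and as box plots. The second is the placebo session, plotted over time in the same two ways.

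On design, section 2.2 states "A single cohort of 15 healthy volunteers will be studied in a 5-way cross-over study (4 doses of LPS versus placebo", and under Regimen Assignment "The randomisation will be balanced over the 5 nasal challenge sequences". Each of the five sequences in Table 1 contains placebo and 1, 10, 30 and 100 μg once. The spacing is given by "A washout time of 12-28 days will be employed between challenges".

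**The concern.** The objective and the data assigned to it do not match. The question is whether the induced ICAM-1 response repeats. The data named to answer it are taken before that session's challenge, or in a session whose challenge is placebo. A subject could have very steady pre-dose values and a flat placebo course and still respond erratically to LPS; the listed displays would not reveal it.

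The design adds a second limit. Repeatability in the usual sense needs the same subject to receive the same dose at least twice, and nobody does. Even a full analysis of the LPS sessions could not separate occasion-to-occasion variation from real differences between subjects in the shape of their dose response.

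At stake is the wording of the conclusion. The model is meant to support later assessment of drugs directed against ICAM-1. A statement that the challenge is reproducible and validated, resting on the displays listed under that name, would say more than they can show.

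**Working it through.** The protocol gives no power, SD or effect size, and sets the sample size by feasibility, so there is no sample-size figure to reproduce. Its count of subjects agrees with Table 1: 5 sequences × 3 = 15, with at least 12 to complete.

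**Same-dose replication.** Replicate df = sum over subjects and LPS doses of (number of times given − 1). Every dose occurs once in every sequence:
- 15 subjects: 15 × 4 × (1 − 1) = 0
- 12 subjects: 12 × 4 × (1 − 1) = 0

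**What the named subsets contain.**
- Pre-dose values: 15 × 5 = 75, giving 15 × 4 = 60 within-subject df (12 × 4 = 48 with 12 subjects). These describe variability of the pre-dose value.
- Pre-dose values that follow an earlier LPS session: sequence 1 starts with placebo, so only periods 3 to 5 qualify (3). Sequences 2 to 5 start with LPS, so periods 2 to 5 qualify (4 each, 16 in all). That is 19 of 25 per set of five sequences; × 3 = 57 of 75.
- Placebo sessions that follow at least one LPS session: all but sequence 1, so 4 × 3 = 12 of 15.
- Post-dose responses from LPS sessions: none, although 15 × 4 = 60 such sessions are planned (12 × 4 = 48 with 12 subjects).

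**What the LPS sessions could support.** Take one log-scale response summary per LPS session and fit subject + period + dose to the four LPS doses. Residual df = sessions − 1 − (subjects − 1) − (doses − 1) − (periods − 1):
- 15 subjects: 60 − 1 − 14 − 3 − 4 = 38
- 12 subjects: 48 − 1 − 11 − 3 − 4 = 29

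The rank of the design matrix built from Table 1 confirms both. The 95% limits for the residual SD, as multiples of its estimate, are √(df/χ²₀.₉₇₅) and √(df/χ²₀.₀₂₅):
- 38 df: √(38/56.90) = 0.82 and √(38/22.88) = 1.29
- 29 df: √(29/45.72) = 0.80 and √(29/16.05) = 1.34

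**What that residual means.** With unreplicated doses its expected variance is the within-subject error variance plus the subject-by-dose interaction variance, plus any carry-over. It therefore tends to overstate test-retest variability. It is also an average over a 100-fold dose range (1 to 100 μg per nostril).

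**The case against.** Section 8.1 calls the study hypothesis generating, and section 8.3.2 only explores reproducibility, with no success criterion. That stands, and it excuses the lack of a formal test. It does not excuse naming data that lack the response in question; an exploratory description still has to describe the right quantity.

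Other displays in section 8.3.2 do show LPS responses: per-subject time plots with one line per dose, summaries of every measure by dose and time, and box plots of ICAM-1 and TNF-α by dose and time. They let a reader judge consistency of response across subjects at each dose, which is one fair sense of a robust challenge. They are not assigned to reproducibility, however, and contain no repeated dose. The optional further analyses are aimed at the ICAM expression profile and could not create replicates either.

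A model belongs in an SAP, which may exist but is not shown. That would answer a complaint that detail is absent. Here the protocol itself fixes which data address reproducibility, and no SAP can add repeated doses.

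A reader might infer that the named subsets contain no LPS exposure, or that none of the 60 LPS sessions contributes. The documents do not support either. Most pre-dose values and placebo sessions come after earlier LPS, and every LPS session supplies its pre-dose value; only the post-dose responses are left out. The pre-dose plots are therefore informative about return to baseline across sessions. A reader might also infer that a later drug study would be sized on baseline variability; nothing in the protocol says so.

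**Conclusion.** The point holds. The reproducibility analysis in section 8.3.2 uses no post-LPS response from the same session, and Table 1 gives 0 df for same-dose replication, so the plan cannot show a reproducible, validated response in the sense of section 2.2. What it can show is stability and return of baseline, the time course under repeated sampling and, through its other displays, consistency of response between subjects.

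It would go too far to say that the trial holds no information on response variability. The LPS sessions support a residual within-subject SD on 38 df (29 with 12 subjects). It would equally go too far to call that SD an upper bound on test-retest variability: it is an estimate with its own error, and if variability differs by dose the pooled value bounds nothing at a given dose.

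The counts rest on Table 1 being followed and all sessions being completed. The interval factors also assume roughly normal residuals with constant variance on the log scale. The study is exploratory and no data are lost by correcting this, so it should be fixed but need not hold up the trial.

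**What to change.** 1. In section 8.3.2, rename the pre-dose displays as stability and return of baseline across sessions, and the placebo displays as procedural time course. Keep both.
2. Add to section 8.3.2 a log-scale model of the post-LPS response summary (ICAM-1 expression, s-ICAM-1, TNF-α) from the four LPS sessions, with subject, period and dose. The per-session maxima already named for the scatter plots would serve as the summary. Report the residual within-subject SD or CV with its 95% CI. State beside it that it mixes within-subject error with subject-by-dose interaction and any carry-over, is pooled over doses, and so tends to overstate test-retest variability without being a bound at any one dose.
3. Reword the hypothesis in section 2 and the first question in section 2.2 so that this trial claims baseline stability and consistency of response, and leaves same-dose test-retest to a later repeat-challenge study.

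The cost is wording in three places and one model per measure on data already to be collected. There are no extra visits and no change to Table 1. The downside is a more modest claim.

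### Intra-subject variability of predose ICAM-1 expression and TNF-α is to be judged from plots only; no within-subject SD is planned, although the scheduled samples would give one

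*Protocol*

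**What the plan says.** Section 2.2 puts reproducibility into the first principal research question: "Can we develop a well tolerated, robust and reproducible (validated) nasal LPS challenge system in terms of ICAM-1 induction". Section 2 gives the purpose, which is to "provide a robust framework for the clinical assessment of future anti-inflammatory therapies directed specifically against ICAM-1".

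Section 8.3.2 says how reproducibility of ICAM-1 expression and TNF-α will be explored. The first subset is "Predose data for each period to explore intra-subject variability". Two displays follow. The first: "Parameter vs. period number will be plotted with a separate line for each subject to explore whether there is a period effect". The second: "Box and whisker plots will also be used to summarise the parameter by period". Data from the placebo session get the same pair of displays over time.

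Two other sentences in the section bear on the point. The general numeric summary is "Each of the measures will be summarised descriptively by dose and time using appropriate summary statistics". The closing sentence is open-ended: "Additional exploratory analyses may be performed to further characterize the expression profile of ICAM following nasal LPS challenge". The section names no within-subject SD, CV, intraclass correlation (ICC) or variance-components model.

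**The concern.** The protocol names a quantity, intra-subject variability, and then chooses tools that do not estimate it. The line plots let a reader see each subject move between periods, but their declared use is to look for a period effect. That is a shift in level common to all subjects, not scatter within a subject. The box plots pool subjects at each period. The numeric summaries by dose and time also run across subjects.

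Whether the unstimulated measure is stable from visit to visit would thus be settled by eye. Two readers of the same plots could reasonably disagree, and nothing could be compared with another laboratory, assay or challenge model.

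**Working it through.** The protocol states no SD, ICC or reproducibility figure, so there is nothing of its own to reproduce. Two questions can be checked.

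**Inputs.** 15 volunteers recruited, at least 12 to complete, five sessions each (Study Design; section 8.2.1). The Study Schedule marks nasosorption and nasal scrape before dosing in every session, so each measure has one predose value per subject and period. Table 1 gives every subject each of the five challenges once.

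**1. What a box plot by period shows.** Write a predose value as subject effect (variance σ_b²) + period effect + residual (variance σ_w²). At a fixed period there is one value per subject, so the variance behind the box is σ_b² + σ_w². With ICC = σ_b²/(σ_b² + σ_w²), within-subject SD = total SD × √(1 − ICC). The documents give no ICC, so a range is assumed, with total SD set to 1:

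| Assumed ICC | Between-subject share of variance | Within-subject SD | Total SD / within-subject SD |
| --- | --- | --- | --- |
| 0.2 | 20% | √0.8 = 0.89 | 1.12 |
| 0.5 | 50% | √0.5 = 0.71 | 1.41 |
| 0.8 | 80% | √0.2 = 0.45 | 2.24 |

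The same box is compatible with within-subject SDs that differ by a factor of two (0.89/0.45).

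**2. Whether the scheduled data can give the figure.** Fit subject + period to the predose values. Residual degrees of freedom = values − 1 − (subjects − 1) − (periods − 1).

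- 15 subjects: 75 − 1 − 14 − 4 = 56.
- 12 subjects: 60 − 1 − 11 − 4 = 44.

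The 95% confidence limits for the within-subject SD are the estimate times √(df/χ²_0.975) and √(df/χ²_0.025).

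- 56 df: √(56/78.57) = 0.84 and √(56/37.21) = 1.23.
- 44 df: √(44/64.20) = 0.83 and √(44/27.57) = 1.26.

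**3. The ICC from the same data.** Exact F interval, one-way layout, k = 5 values per subject: F = 1 + 5·ICC/(1 − ICC). Divide F by the upper 2.5% point of F on (n − 1, 4n) df to get L, and multiply it by that of F on (4n, n − 1) df to get U. The limits are (L − 1)/(L + 4) and (U − 1)/(U + 4).

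| Estimated ICC | 95% CI, n = 12 | 95% CI, n = 15 |
| --- | --- | --- |
| 0.5 | 0.25 to 0.77 | 0.27 to 0.75 |
| 0.8 | 0.62 to 0.93 | 0.64 to 0.92 |

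The within-subject SD is well determined. The ICC is not, because it also rests on a between-subject variance estimated from only 12 to 15 people.

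**The case against.** The best defence is that the choice of estimator normally belongs in a statistical analysis plan, which is not available here. Section 8.1 calls the study exploratory, section 8.3.2 permits further analyses, and the five predose values will exist whatever is written now. All of that is true, and it limits the severity. It does not remove the point. The protocol does not leave the method open: it names the target and lists the tools. The permissive closing sentence is optional and concerns the ICAM expression profile, not reproducibility. An SD with an interval is description, so the exploratory label is no bar to it.

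The defence is also right that the per-subject lines do show within-subject change, and that the box plots do what their own sentence says, namely summarise by period. They are sound displays. They just do not yield the quantity named above them.

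Three stronger readings are tempting, and the documents do not support them.

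- A reader might infer that the box plots mainly show between-subject spread. That needs an ICC above 0.5, and the protocol gives no variance from which to judge.
- A reader might infer, from the purpose in section 2, that the predose SD is the figure that sizes a later anti-ICAM-1 trial. Such a trial would compare LPS-induced responses. The predose SD describes the unstimulated nose.
- A reader might infer that the trial will end without any such figure. It is only not planned: the data permit it, and an analysis plan may add it.

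**Conclusion.** The point holds in a limited form. For predose ICAM-1 expression and TNF-α, section 8.3.2 plans displays and no estimate of intra-subject variability, although reproducibility is part of the primary objective. The planned samples would fix the within-subject SD to within about 0.83 to 1.26 times its estimate with 12 completers, and 0.84 to 1.23 times with 15.

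This precision assumes one usable predose value per subject and period, roughly normal residuals on the analysis scale, and a within-subject variance common to all subjects. Missing or undetectable values would widen it.

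The estimate has limits of its own. It is baseline variability. Predose values in periods 2 to 5 follow earlier challenges, so any effect that outlasts the 12 to 28 day washout would be counted in it. Same-dose reproducibility of the LPS response cannot be estimated from this design at all, because no dose is repeated within a subject; the residual of a crossover model would mix error with subject-by-dose interaction. The defect is a cheap gap in the analysis, and no data are lost by it.

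**What to change.** Add to the reproducibility paragraph of section 8.3.2, for predose ICAM-1 expression and TNF-α only:

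- Fit a model with subject as a random effect and period as a fixed effect, on the log scale if the measure is transformed.
- Report the within-subject SD, or the CV derived from it, with a 95% confidence interval.
- Report the ICC with its interval as a secondary figure, noting its imprecision at 12 to 15 subjects.
- Keep the line plots and box plots as displays.
- State that the estimate describes baseline variability, that any carry-over from earlier challenges would enter it, and that same-dose reproducibility of the LPS response cannot be estimated because each dose is given once per subject.

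The cost is one simple model for each of two measures and a few sentences of text. Sampling, design and sample size do not change.
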